##### Problem-solving style

Social Problem-Solving Inventory-Revised Short Form (SPSI-R:SF) [46, 47]

The SPSI-R:SF is a 25-item, self-report questionnaire measuring abilities in problem-solving: positive problem orientation (PPO), negative problem orientation (NPO), rational problem-solving (RPS), impulsivity-carelessness style (ICS), and avoidant style (AS). Each item is rated on a 5-point Likert scale, and scores are computed for each of these subscales, as well as a global score for total inventory. Higher scores on the NPO, ICS, and AS reflect a more maladaptive approach to problem-solving, whereas higher scores on the PPO and RPS indicate more adaptive strategies. Studies have reported good construct validity, internal consistency (with Cronbach’s alpha coefficients ranging from .73 to .86), and test–retest reliability (with the intraclass correlation coefficients ranging from .74 to .87) [46, 47].

##### Emotional dysregulation

Difficulties in Emotion Regulation Scale (DERS) [4, 48]

The DERS is a 36-item self-report questionnaire measuring different dimensions of ED: non-acceptance of emotional responses; difficulties engaging in goal-directed behavior; impulse control difficulties; a lack of emotional awareness; limited access to emotional regulation strategies; and a lack of emotional clarity. Each item is rated on a 5-point Likert scale, and scores are computed for each of these subscales, as well as a global score for total inventory. The DERS is the most comprehensive measure of ED to date and exhibits good reliability and validity when administered to adults [4]. Specific analyses also confirmed the reliability and validity of the DERS in adolescents (Cronbach’s alpha coefficients ranged from .76 to .89 for the subscales) [49]. The Italian version of the DERS showed adequate and comparable properties [48].

##### Depression

Patient Health Questionnaire-9 (PHQ-9) [50]

The PHQ-9 is a 9-item, self-report questionnaire measuring depression severity. Each of the 9 items can be scored from 0 (not at all) to 3 (nearly every day); a total score is computed as the sum of the nine items. Studies have shown that the PHQ-9 has excellent internal validity (with Cronbach’s alpha coefficient higher than .85) and test–retest reliability. Different levels of severity of depression can be distinguished according to the cutoff [50].

##### Anxiety

Screen for Child Anxiety Related Emotional Disorders (SCARED) [51, 52]

The SCARED is a 38-item, self-report questionnaire measuring different manifestations of anxiety: panic disorder, generalized anxiety disorder, separation anxiety disorder, school anxiety, and social anxiety. The SCARED showed good internal consistency and test–retest reliability [51]. The Italian version of the SCARED was found to be a valid screening instrument [52].

##### Impulsivity

Barratt Impulsiveness Scale–Brief (BIS-Brief) [53]

The BIS-Brief is an 8-item, self-report questionnaire that establishes the personality construct of impulsiveness in adolescents. The BIS-Brief showed good reliability and construct validity [53].

At baseline, data on sociodemographic data—such as information on number of visits with mental health professionals, pharmacological treatments, lifestyle (sleep quality, leisure activities, number of friends), and academic performance—will be collected. In addition, at baseline, the following instruments will be administered to assess psychosocial domains associated with ED: the Personality Inventory for DSM-5 [54] for personality traits; the Childhood Trauma Questionnaire [55] for early adverse experiences; the Adolescent Stress Questionnaire [56] for stressful life events in the previous year; the School Climate Measure [57] for school climate; the Child and Adolescent Social Support Scale [58] for relationships with classmates; and the Family Assessment Device [59] for family functioning.

### Participants’ timeline {13}

Details about the timeline and assessments are reported in Table 1.

### Sample size {14}

The primary outcome measures will be represented by changes in impulsive behaviors (established by the Checklist for Impulsive Behaviors) and by changes in emotional regulation skills (determined by the DBT-Ways of Coping Checklist).

Precisely, the outcome will be evaluated in terms of change (pre/post) in percentage of “yes” answers in the two groups (treated and control), where “yes” is defined as a difference of at least one category toward improvement from baseline. More specifically, the scores of the Checklist for Impulsive Behaviors are measured on a Likert scale. Therefore, a “yes” answer implies a decrease in the frequency of impulsive behavior; for example, from the category “two or three times a week” to the category “one time a week.” In a similar manner, a “yes” answer for the DBT-Ways of Coping Checklist means a decrease in the use of dysfunctional skills; for example, from the category “regularly used” to “sometimes used,” or vice versa for functional skills.

We assumed that at baseline, there would be a between-group difference by chance of 7% (i.e., 1/15 yes answers, where 15 is the total number of checklist items) on the Checklist for Impulsive Behaviors and that this difference would increase by up to 13% (i.e., 2/15 yes answers) after the intervention. Based on these assumptions and applying a two-sided test for paired binomial proportions, with a significance level equal to 0.05 and a power of 0.8, the estimated sample size was *n* = 340 (170 per group). Moreover, considering a drop-out rate of 20%, the minimum sample size (MSS) reached *n* = 426 (213 per group).

In the same way, we assumed that on the DBT-Ways of Coping Checklist, there would be a difference by chance of 7% (i.e., 4/59 yes answers, where 59 is the total number of the checklist DBT items) at baseline, and that this difference would increase by up to 20% (i.e., 12/59 yes answers) after the intervention. This last hypothesis was made considering that, given the focus of treatment, we expected a greater change in emotional regulation skills than in dysfunctional behaviors. Based on these considerations and applying a two-sided test for paired binomial proportions, with a significance level equal to 0.05 and a power of 0.8, we reached an estimated sample size of *n* = 84 (42 per group).

In sum, due to both the outcome measures and related sample size estimations, the final sample size needed was 426 students.

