### Outcomes {12}

#### Primary outcomes

##### Emotional regulation skills

DBT-Ways of Coping Checklist (DBT-WCCL) [45]

The DBT-WCCL is a 59-item self-report questionnaire measuring the frequency of DBT skills use (DBT Skills Subscale, 38 items) and dysfunctional coping strategies (Dysfunctional Coping Subscale, 21 items). Participants will be asked to indicate, on a 4-point Likert scale, the frequency of use of each skill in the previous month (i.e., never used, rarely used, sometimes used, or regularly used). The scale showed good internal consistency (Cronbach’s alpha coefficients for the subscales ranged from .84 to .96) and content validity [45]. For our primary outcome analysis, we will assess the difference between the two groups in terms of the proportion of participants categorized as “improved” post-intervention. Specifically, we will consider as “improved” those participants with a difference of at least one category, toward improvement, from the baseline to post-intervention in the frequency of use of functional skills. Intervention efficacy will be defined by a difference of at least 20% (i.e., 12/59 items) of improvement between groups after the intervention.

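### The DBT-WCCL primary outcome is defined on the 38 functional items in one section and on all 59 items in another, and the 20% efficacy threshold is written over 59

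*Protocol article*

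**What the plan says.** The protocol article describes the DBT-WCCL as 59 items in two subscales: DBT Skills (38 items) and Dysfunctional Coping (21 items).

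- **Outcomes {12}, Emotional regulation skills.** The primary analysis compares the share of students classed as improved. A student is improved if there is a shift of at least one category "from the baseline to post-intervention in the frequency of use of functional skills". The next sentence reads: "Intervention efficacy will be defined by a difference of at least 20% (i.e., 12/59 items) of improvement between groups after the intervention".
- **Sample size {14}.** The outcome is restated as the percentage of *yes* answers. A *yes* "answer for the DBT-Ways of Coping Checklist means a decrease in the use of dysfunctional skills", "or vice versa for functional skills". The assumed chance difference between groups at baseline is 7%, explained as "4/59 yes answers, where 59 is the total number of the checklist DBT items". The difference after the intervention is 20%, explained as 12 of 59.
- **Objectives {7}, hypothesis 2, and the Abstract.** Both speak only of use of emotional regulation skills. Neither includes a fall in dysfunctional coping in this outcome.

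**The concern.** One of the two primary outcomes has two item sets. The Outcomes section counts functional items. The sample size section counts functional items that rise and dysfunctional items that fall. The Outcomes section is also at odds with itself, because its functional-only definition is followed by a threshold over the whole checklist. The figure 59 is no slip of the pen: it recurs in the sample size section for both assumed differences and is explained there as the full item count.

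This is a conflict between two stated definitions, not detail left to an analysis plan. An analysis plan could adopt either one and claim to follow the protocol. What is at stake is whether the efficacy criterion is met, and what a positive result would mean: more skill use, or some mixture of more skill use and less dysfunctional coping.

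**Working it through.** **Inputs.** Item counts 38, 21 and 59, and the threshold of 20% (12/59): Outcomes {12}. Assumed differences of 7% (4/59) and 20% (12/59), two-sided significance level 0.05, power 0.80, n = 84 (42 per group), n = 340 for the Checklist for Impulsive Behaviors (CIB), and 20% drop-out: Sample size {14}.

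**1. The plan's own sample size.** A one-sample proportion formula, with its result doubled for two groups, reproduces the DBT-WCCL figure exactly and the CIB figure closely:

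n per group = [1.96·√(p0(1−p0)) + 0.842·√(p1(1−p1))]² / (p1−p0)²

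- DBT-WCCL, 0.07 and 0.20: (0.500 + 0.337)² / 0.0169 = 41.4, so 42 per group and 84 in total, as stated.
- CIB, 0.07 and 0.13: (0.500 + 0.283)² / 0.0036 = 170.4 per group, against 170 stated.
- Drop-out: 170 / 0.8 = 212.5, so 213 per group and 426 in total, as stated.

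With the unrounded fractions 4/59 and 12/59 the formula gives 37.6, so 38 per group and not 42. The plan's figure therefore appears to rest on the rounded percentages and not on item counts. Whether this formula suits the paired test that the plan names is a separate question.

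**2. What the item counts mean on each base.**

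| Quantity | Over 59 | Over 38 |
|---|---|---|
| 12 items | 20.3% | 31.6% |
| 4 items | 6.8% | 10.5% |
| 20% of the items | 11.8 | 7.6 |

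The 21 dysfunctional items, 21/59 = 36% of the checklist, are in or out depending on the section.

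**3. Can the choice change the result?** Take the threshold as a difference in the percentage of items improved. The mean counts per student below are invented, to show only that the two definitions can disagree.

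- Treated 14 functional + 2 dysfunctional, control 6 + 2. Functional only: (14 − 6)/38 = 21.1%, meets 20%. All items: (16 − 8)/59 = 13.6%, fails.
- Treated 10 + 9, control 6 + 1. Functional only: (10 − 6)/38 = 10.5%, fails. All items: (19 − 7)/59 = 20.3%, meets.

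The result can turn in either direction.

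**4. Sample size if the outcome is the 38-item subscale** (formula of step 1).

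- 7% and 20% kept: 84 in total.
- Nearest whole items, 3/38 and 8/38: 43.9, so 44 per group and 88 in total.
- Counts 4 and 12 carried over to 38 (10.5% and 31.6%): 22.2, so 23 per group and 46 in total.

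All three lie far below the 340 that the CIB requires before drop-out.

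**The case against.** Three objections deserve an answer.

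*The analysts are blinded.* A reader might infer that someone could pick the favourable item set after unblinding. The documents do not support that: the blinding sections {17a} and {17b} say that data analysts are blinded and that unblinding will not occur. What remains is narrower. Blinding to arm does not settle which items count, and the choice could still be made once the data are in view.

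*The trial's size is not at stake.* A reader might also infer that the sample size was built on the wrong items. Step 1 indicates that 84 comes from the percentages 7% and 20% alone, and the total of 426 comes from the CIB. This objection stands in full.

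*The percentages in step 2 assume that the unit is items.* The Outcomes section compares a proportion of participants, and 20% of participants does not translate into 7.6 or 12 items. This also stands, and it exposes a second conflict in the same sentences: a participant-level proportion carries an item-count threshold. It does not remove the first conflict, because whether a student counts as improved still depends on which items are examined.

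**Conclusion.** The contradiction is real and concerns the definition of a primary outcome. The two sections differ over 21 of 59 items, and the threshold's item gloss does not fit the functional-only definition that it follows. Read as a share of items, 12 items is 20.3% or 31.6%, and the same data can pass on one reading and fail on the other. The size of any such effect in the actual trial cannot be known from the documents; the counts in step 3 are assumptions.

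The consequence is limited to how the outcome is defined and interpreted. The planned total of 426 does not change. The point should be settled before analysis, but it does not put the design in doubt.

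**What to change.** Before analysis, state one definition in both Outcomes {12} and Sample size {14}:

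1. Name the 38-item DBT Skills Subscale as the item set. It matches the Abstract, hypothesis 2 and the definition of improvement in the Outcomes section.
2. Report the 21-item Dysfunctional Coping Subscale separately, outside the primary outcome.
3. Remove the glosses 12/59 and 4/59, or restate them on 38 items.
4. Say whether the 20% is a difference in the proportion of participants improved or in the percentage of items improved. Without this, changing the denominator would still leave an item count attached to a proportion of participants.
5. Restate the DBT-WCCL calculation on the chosen basis (84 if 7% and 20% are kept, 88 with 3/38 and 8/38), and note that 426 is unchanged.

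Both subscales come from the same questionnaire, so data collection does not change. The cost is wording in two sections. Under the amendments section {25}, the Ministry of Health and the Ethics Committee must also be notified and the approved change uploaded to the trial registration site.

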### Trial design {8}

This is an interventional, parallel assignment, two-arm, cluster randomized trial. The classes of students will be randomized into a psychoeducational intervention (experimental group) or control condition (control group). All participants will be assessed at baseline, post-intervention, and at the 3- and 6-month follow-up points by using self-report questionnaires. In addition, salivary samples will be collected at baseline and post-intervention. Details on the timeline and assessments are reported in Table 1.

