## Methods: participants, interventions, and outcomes

### Study setting {9}

A total of 20 school classes will be recruited among the high schools of Brescia (Northern Italy), for a total of approximately 440–460 students (considering approximately 22–23 students per school class) attending several high schools in the city. Each school will enroll an even number of classes to be randomized to the experimental or control conditions.

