## Assignment of interventions: allocation

### Sequence generation {16a}

After enrollment, the statistician will randomly assign the classes within each school to experimental or control conditions. More specifically, a random sequence of strings (of length equal to the number of school classes) with labels “Experimental” or “Control” will be generated by a computer code, with a ratio of 1:1 (experimental vs. control). The classes will then be linked to the random sequence following their alphabetic order.

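### The trial randomises 20 classes, but the sample size treats students as independent, so the stated power of 0.8 for the Checklist for Impulsive Behaviors holds only if the class intraclass correlation is close to zero

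*Protocol article*

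**What the plan says.** Trial design {8} states: "This is an interventional, parallel assignment, two-arm, cluster randomized trial". Study setting {9} plans 20 classes, "for a total of approximately 440–460 students (considering approximately 22–23 students per school class"), and adds: "Each school will enroll an even number of classes to be randomized to the experimental or control conditions". Under Sequence generation {16a}, "the statistician will randomly assign the classes within each school to experimental or control conditions", "with a ratio of 1:1 (experimental vs. control"). The class is therefore the unit of randomisation, with about ten classes per arm.

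Sample size {14} derives the size for each of the two primary outcomes from a two-sided test for paired binomial proportions. For the CIB it moves from 7% to 13%: "with a significance level equal to 0.05 and a power of 0.8, the estimated sample size was" 340 (170 per group), raised to 426 (213 per group) for 20% drop-out. For the DBT-Ways of Coping Checklist (DBT-WCCL) it moves from 7% to 20% and obtains 84 (42 per group). The larger figure, from the CIB, becomes the size of the trial. The section mentions no ICC, design effect, class size or number of classes.

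**The concern.** Students in one class share teachers and peers and, in the experimental arm, the same sessions. If their outcomes are correlated, 340 students in 20 classes carry less information than 340 independent students, and a power computed for independent students is too high. The CIB is where this bites, because it sets the sample size and has no reserve.

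At stake is how a null CIB result would be read. Taken with a stated power of 0.8, it would count as fair evidence against an effect on impulsive behaviours, when it might only reflect low power. Under Explanation for the choice of comparators {6b}, the article intends the results to support a place for such curricula in school scheduling, so the misreading would have consequences.

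**Working it through.** **Inputs from the article.** Two-sided alpha 0.05; power 0.80; CIB 7% to 13%; DBT-WCCL 7% to 20%; drop-out 20%; final size 426 (all Sample size {14}). 20 classes and 440–460 students (Study setting {9}).

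**Step 1: reproduce the stated figures.** A one-sample normal-approximation formula, applied per group, reproduces both:

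n = [(1.960·√(p0(1−p0)) + 0.842·√(p1(1−p1))) / (p1−p0)]²

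- CIB: √(0.07·0.93) = 0.2551 and √(0.13·0.87) = 0.3363, so n = [(0.5001 + 0.2830)/0.06]² = 170.4 (stated 170).
- DBT-WCCL: √(0.20·0.80) = 0.4, so n = [(0.5001 + 0.3366)/0.13]² = 41.4, rounded up to 42 (stated 42).
- Drop-out: 170/0.8 = 212.5, rounded up to 213 per group, 426 in total.

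The chain closes exactly, so no clustering factor is hidden in 426.

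**Step 2: add the design effect.** With 340 completers in 20 classes, m = 340/20 = 17 per class. Design effect DE = 1 + (m−1)·ICC = 1 + 16·ICC. The effective number per group is n = 170/DE. On the article's own formula,

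power = Φ{[0.06·√n − c·0.2551] / 0.3363},

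with c = 1.960 (normal), or c = 2.101 (t on 20 − 2 = 18 degrees of freedom).

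The ICC values are assumptions, because the article gives none.

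| ICC | DE | Effective total N | CIB power, normal | CIB power, t critical value (18 df) |
|---|---|---|---|---|
| 0 | 1.00 | 340 | 0.80 | 0.77 |
| 0.01 | 1.16 | 293 | 0.75 | 0.71 |
| 0.02 | 1.32 | 258 | 0.70 | 0.67 |
| 0.05 | 1.80 | 189 | 0.60 | 0.56 |

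**Step 3: does the planned 440–460 make up for it?** After 20% drop-out, 352–368 students remain, or 17.6–18.4 per class. An effective total of 340 requires ICC ≤ (352/340 − 1)/16.6 = 0.002 at 440 students, or (368/340 − 1)/17.4 = 0.005 at 460. At 460 students, CIB power on the normal formula is 0.77 at ICC 0.01 and 0.61 at ICC 0.05.

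**Step 4: the DBT-WCCL.** It needs 84 students on the same formula. With 340 analysed, the tolerable design effect is 340/84 = 4.05, so the ICC can reach 3.05/16 = 0.19 before power falls below 0.8.

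**The case against.** Several points can be made for the plan.

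- *Within-school allocation and change from baseline reduce the relevant ICC.* They may. Allocation within schools can take between-school variation out of the comparison, though not variation between classes of the same school. The article neither claims nor quantifies either gain, so they bear on which ICC is plausible but do not support the 0.8.
- *More than 426 students are planned.* True, but step 3 shows how little that reserve covers.
- *Generalised mixed models are planned.* Statistical methods {20a} does not name class as a random effect, and modelling the clustering would not restore power left out of the sample size.
- *An article condenses the full plan.* Here the whole derivation is given and closes without a clustering term, so this is not a detail left to another document.
- *The power figures rest on a one-sample formula.* This stands. The Impulsive behaviors entry under Outcomes {12} plans a between-group comparison of proportions. Read as two independent groups at 7% and 13%, 170 per arm gives only about 0.45 power before any clustering. The table therefore shows the loss relative to the article's own starting point, not the power of the planned comparison.

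A reader might also infer that both primary outcomes lose their power, or that the trial could not detect the planned effect. Neither follows. On the article's formula the DBT-WCCL is well protected, and at ICC 0.01–0.02 the loss for the CIB is modest.

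**Conclusion.** The omission is certain: classes are randomised, and the calculation that yields 426 assumes independent students. For the CIB, the stated power of 0.8 is not delivered unless the class ICC is close to zero, at most about 0.005 even with 460 students enrolled.

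The size of the shortfall is conditional. It depends on an assumed ICC, on 17 completers in each class, and on a one-sample formula that does not match the planned comparison. On those terms CIB power is about 0.75 to 0.60 for ICCs of 0.01 to 0.05, or about 0.71 to 0.56 with the t critical value. The right conclusion is that the trial may be underpowered for the CIB and that a null CIB result may reflect low power.

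The point does not extend to the DBT-WCCL on the article's own arithmetic. That reassurance uses the same one-sample formula, so it too should be confirmed on a between-group basis.

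**What to change.** In Sample size {14}:

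1. State an assumed class ICC with a range, for example 0.01–0.05, and its basis.
2. Use a formula for the between-group comparison of proportions given under Outcomes {12}. Inflate its variance by 1 + (m−1)·ICC with m of about 17 completers per class, and take the critical value from a t distribution with at most 18 degrees of freedom. If within-school allocation or baseline adjustment is expected to lower the ICC, say so and quantify it.
3. Report the power, or the detectable difference, that 20 classes deliver for each primary outcome across that range.
4. Withdraw the 0.8 claim for the CIB.

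The cost is a rewritten section and a less favourable stated power. No extra recruitment is required, because the change corrects what is claimed for the classes already planned.
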